## Abstract

**Methods::**

In this RCT, an estimated number of 200 patients with BPH will be enrolled from Shanghai Fourth People’s Hospital, China. They will be assigned to either the combined therapy group or the conventional western medicine group in a ratio of 1:1. The International Prostate Symptom Score (IPSS) will be assessed as the primary outcome, other parameters, including the post-voiding residual urine volume, maximum flow rate (Qmax), and average flow rate (Qave), voiding time, and time to maximum flow, are secondary outcomes.

**Discussion::**

Results of this study will provide the theoretical basis for clinicians to select combined therapy or conventional western medicine treatments for BPH patients based on the efficacy of these therapies.

**Trial registration::**

chictr.org.cn, ID: ChiCTR2000030504/ChiMCTR2000003082. http://www.chictr.org.cn/edit.aspx?pid=47719&htm=4, Registered on 5th March 2020.

## 1. Introduction

Benign prostatic hyperplasia (BPH), a medical condition that is due to the excessive proliferation of the glandular epithelial and stromal cells, is common in elderly males.^[1]^ Symptoms of BPH include hesitancy, forceful urination with a slow urination stream, frequent urination, etc. Other symptoms may occur when this condition is complicated, including urgency to urinate, irritating feeling.^[2]^ The prevalence of BPH is nearly 50% among males 50 years or older^[3,4]^ and almost all males by 90.^[3]^ As the aging population surges, the incidence and the total number of BPH patients will keep rising.^[5]^

BPH is clearly associated with age and the increment of testosterone (T) and dihydrotestosterone in the body, but the etiology is still unknown. It is a consensus that excessive proliferation of the prostate stroma is the primary mechanism, which leads to the increased mass in the transition zone of the prostate, compressing the urinary tract.^[6,7]^ Others proposed that BPH is the result of prostate inflammation and altered metabolic processes due to the frequent presence of this condition with prostate inflammation and metabolic syndromes.^[8–13]^

Medical treatments for BPH are targeting the pathogenic mechanisms, such as conservative treatment with medications and surgical removal of the excessive tissue. The latter is only for refractory patients. However, none of the treatments can cure this condition and they all have side effects or complications to different degrees.

Alpha blockers are commonly prescribed to BPH patients. This type of drugs, like doxazosin and tamsulosin, can mitigate the tension of the smooth muscle cells of the prostate and the bladder,^[14]^ resulting in less constriction of the urinary tract. Consequently, symptoms are ameliorated and the urinary flow rate increased. Due to the presence of alpha receptors in the vascular system, alpha blockers have significant side effects related to blood vessel dilation, such as orthostatic hypotension, dizziness, and fatigue.

5α-reductase inhibitors are also key medicines. They can inhibit the activity of enzymes that catalyze the transition from testosterone to dihydrotestosterone. The latter can effectively suppress cell proliferation of the prostate gland and mitigate the symptoms.^[15]^ Finasteride and dutasteride are two commonly prescribed medications. Due to the importance of male hormone in sexual behavior, their side effects, such as sexual dysfunction, may stop their use for some younger patients. Reports also suggested that intake of these two medications with lower dosages is better than either of them taken alone in relieving symptoms.^[10,16]^

Phosphodiesterase type 5 inhibitors, known to increase the level of nitric oxide and to relax the urinary tract, are also used to treat BPH patients.^[17–21]^ Combination of phosphodiesterase type 5 inhibitors with alpha blockers has shown better tolerance and therapeutic effect than alpha blockers alone due to its capacity in alleviating erectile dysfunction and improving outcomes of BPH patients.^[22–25]^

Surgical therapy has its own advantage in rapidly relieving the symptoms. However, pain and other possible complications also inflict these patients.

In traditional medicine, acupuncture has been used to treat such patients in Asian countries based on the traditional Chinese medicine (TCM) theory. It is interpreted in a way that urination is relying on the “Qi” of the Kidney. In aging males, “Qi” of the kidney is supporting the urination behavior and is slowly diminished. Therefore, it takes a longer time for these patients to urinate than younger adults. As is recorded in TCM theory, “Qi” is known to circulate the blood flow. When “Qi” is weak, blood stasis will occur, which curtails the supply of nutrition and oxygen to the prostate tissue and aggravates the symptoms (see review of ref.^[26]^). Hence, it is necessary to increase “Qi” to restore the function of the prostate. A myriad of studies have been published in China testing the effectiveness of herbs, acupuncture, or moxibustion as primary therapies for BPH patients (see review of ref.^[27]^). However, the majority of these studies were case reports and few were randomized controlled trials (RCTs). Among acupuncture studies, the selection of acupoints or the use of acupuncture with herbs was the main stream research. Few studies combined acupuncture with moxibustion to treat BPH. It is, therefore, our aim to answer this question by designing an RCT to test whether the combined therapy of acupuncture and moxibustion, which is able to reduce the size of the prostate and has fewer side effects, is as effective as conventional medical treatments.

### 1.1. Our hypothesis

Combined use of moxibustion and acupuncture applied to a few acupoints that are known to increase “Qi” of the kidney will be as effective as western medical therapies in managing BPH, or even better than them.

### 1.2. Objectives

To test whether the combined therapy with acupuncture and moxibustion is as effective as conventional western medical therapies in managing BPH using an RCT.

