#### 2.4.1. Primary outcomes

The IPSS at 18 weeks after the start of the trial will be used to assess the severity of symptoms and treated as the primary outcome. The IPSS has 8 questions with each of the first 7 questions scored 0 to 5, resulting in a sum of 0 to 35. These questions are about urinary symptoms for patients to tick one out of six answers. These include: frequency, incomplete emptying, intermittency, weak stream, urgency, straining, and nocturia. A total score of <7 is ranked mild, 8 to 19 moderate, and 20 to 35 severe. The 8th question is about the quality of life perceived by the patients, which ranges from 0 to 6, corresponding to delightful to terrible quality of life.

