### 2.6. Sample size

To calculate the sample size, results of our pilot study were used to estimate the number of patients we need for this trial. In our RCT, the efficacy of the combined therapy and the conservative medical treatment was 80% and 60%, respectively, 0.05 for α, 0.8 for 1-β, 20% for the dropout during the follow-up. Eighty patients in each group are required as calculated using the Two Independent Proportions (Null Case) Power Analysis (Pass 11 software). A 25% dropout rate is estimated. Finally, 100 patients in each group are needed.

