### 2.9. Statistical method

Results collected will be initially validated by two investigators before statistical analyses. Data analysis will be conducted using IBM SPSS (version 20.0) for Windows (SPSS Inc., Chicago, IL) by a statistician who is blinded to patients’ information. Continuous variables will be presented as mean ± SD or median with an interquartile range (IQR). Information of patients at enrollment will be compared using the Mann-Whitney *U* test or using the *t* test for continuous variables, and the Fisher’s exact test or χ^2^ for categorical variables. Two-side Student’s *t* test will be used to compare continuous variables like IPSS, maximum flow rate, voiding time, average flow rate, post-voiding residue urine volume, and time to maximum flow 18 weeks after treatment. Longitudinal analysis of IPSS, Qmax, voiding time, post-voiding residual urine, Qave, and time to maximum flow were done with a GLMM approach, accommodating data with nonequidistant repeated measures of time and missing values. *P* < .05 (two-sided) is considered statistically significant.

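### The objective asks whether the combined therapy matches drug treatment, but the sample size and analysis test only for a difference and set no margin, so a non-significant result would not answer it

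*Protocol article*

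**What the plan says.** All references are to the protocol article.

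- **Question.** Section 1.2 gives the objective as testing whether the combined therapy "is as effective as conventional western medical therapies in managing BPH". The last paragraph of the Introduction states the same aim. The hypothesis in section 1.1 is that the combined therapy "will be as effective as western medical therapies in managing BPH, or even better than them".
- **Primary outcome.** Section 2.4.1 names the IPSS at 18 weeks.
- **Sample size.** Section 2.6 assumes efficacy of 80% with the combined therapy and 60% with conventional treatment, α of 0.05 and power of 0.8. It obtains 80 per group from a "Two Independent Proportions (Null Case) Power Analysis" and raises this to 100 per group for dropout.
- **Analysis.** Section 2.9 says that a two-sided Student's t "test will be used to compare continuous variables like IPSS" at 18 weeks. Longitudinal analyses "were done with a GLMM approach, accommodating data with nonequidistant repeated measures of time and missing values". Significance is judged at two-sided P < .05.

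The article states no equivalence or non-inferiority margin and no confidence-interval rule.

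**The concern.** A claim that one therapy is as good as another, or better, is a non-inferiority claim with superiority as a second step. To support the first part, the data must exclude a deficit larger than some stated amount. The plan instead takes zero difference as the null hypothesis, both for the sample size and for the test. Such a test can reject equality but cannot establish it.

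The hypothesis type and any margin determine the sample size, and this article states its hypothesis, its sample-size method, its test and its significance rule. The mismatch is therefore between statements in the text, and is not a detail left to an analysis plan that is not shown.

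At stake is how a non-significant result would be read. The comparator is active drug treatment, and the abstract says that clinicians will use the results to choose between the two therapies. If P is .05 or above, the objective as worded invites a conclusion that the analysis cannot support.

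**Working it through.** **1. Which question does the sample size answer?** Inputs from section 2.6: 0.80 and 0.60, α = 0.05, power 0.80.

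- Pooled, two-sided: n = [1.960·√(2·0.7·0.3) + 0.842·√(0.8·0.2 + 0.6·0.4)]² / 0.2² = (1.270 + 0.532)² / 0.04 = 81.2, so 82.
- Unpooled, two-sided: n = 0.40·(1.960 + 0.842)² / 0.04 = 78.5, so 79.
- Arcsine: 80.3. The exact power of the uncorrected two-sided chi-square test at 80 per group is 80.1%.
- One-sided, pooled: 64, which does not match.

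The stated 80 is therefore reproduced, to within 2 patients, by a two-sided test of zero difference. No margin enters it.

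**2. What would a non-significant result show on the response scale?** Suppose the combined therapy is truly worse, 50% against 60%, with 80 evaluable per group.

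- SE under the null = √(2·0.55·0.45/80) = 0.0787; SE under the alternative = √((0.24 + 0.25)/80) = 0.0783.
- Power = Φ[(0.10 − 1.960·0.0787)/0.0783] = Φ(−0.69) = 0.244.

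A 10-point deficit would be detected about 24% of the time and missed about 76% of the time. With both groups at 60%, the 95% CI half-width is 1.96·√(2·0.24/80) = 0.152, about 15 percentage points.

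**3. The same on the primary outcome.** The document gives no IPSS SD, so SDs of 5 to 8 are assumed. With 80 per group, the noncentrality for a true deficit of M points is (M/SD)·√40, with 158 degrees of freedom and critical value 1.975. The probability that the two-sided t test is non-significant is:

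| True deficit | SD 5 | SD 6 | SD 7 | SD 8 |
|---|---|---|---|---|
| 2 points | 29% | 45% | 57% | 65% |
| 3 points | 3.5% | 12% | 23% | 35% |
| 4 points | 0.1% | 1.3% | 5.1% | 12% |

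**4. Would 80 per group serve a non-inferiority test?** With a true difference of zero, one-sided 2.5% and margin M, power = 1 − F(1.975; 158 df, noncentrality (M/SD)·√40). Margins are assumed, since none is given.

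| Margin | SD 5 | SD 6 | SD 7 | SD 8 |
|---|---|---|---|---|
| 2 points | 71% | 55% | 43% | 35% |
| 3 points | 97% | 88% | 77% | 65% |
| 4 points | 99.9% | 98.7% | 94.9% | 88% |

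For 80% power by the normal formula, n = 2·SD²·(1.960 + 0.842)²/M². A 2-point margin needs 99, 142 and 193 evaluable per group at SDs of 5, 6 and 7; a 3-point margin needs 44, 63 and 86.

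**The case against.** The best defence is that this is a superiority trial with a loosely worded objective. Section 2.6 assumes a 20-point advantage for the combined therapy. Section 2.1 and the opening of the Discussion state the aim neutrally, as a comparison of efficacy. The limitations paragraph treats not showing a benefit as a failure. This is a fair reading and it points to the simpler remedy. It does not remove the conflict, because the Introduction, sections 1.1 and 1.2, and the Discussion's expectation of similar or better efficacy all say otherwise.

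Several stronger readings are tempting, and the document does not support them:

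- **That the trial cannot support its hypothesis at all.** A significant result favouring the combined therapy would support it, and that is the case for which section 2.6 is powered. Only a non-significant result leaves the objective unanswered.
- **That the investigators plan to read P ≥ .05 as equality.** Nothing in the article says so. The argument that dropout or noisy data would make the claim easier to reach depends on that inferred misuse.
- **That the t test is the only analysis.** A GLMM is also planned, though it too has no margin.
- **That a deficit of 0.2 or 0.3 SD, missed 76% or 53% of the time, shows an inferior therapy passing.** At an assumed SD of 6 these are 1.2 and 1.8 points, smaller than each of the 2-, 3- and 4-point margins examined above. A deficit as large as the margin is the relevant case, and it is often missed much less frequently.
- **That adding a margin is free.** The second table shows that this depends on the margin and the SD.

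**Conclusion.** The concern holds in a limited form. The stated objective and hypothesis do not match the sample size and analysis, and a non-significant result would not show that the combined therapy is as effective as drugs.

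How much this matters depends on quantities that the document does not give. On the response scale used for planning, a 10-point deficit from 60% would go undetected about three times in four. On IPSS, with 80 evaluable per group and assumed SDs of 5 to 8, the chance of missing a true deficit is 29% to 65% for 2 points, 3.5% to 35% for 3 points and 0.1% to 12% for 4 points. The problem is therefore serious if deficits of 2 or 3 points matter, and smaller if only larger ones do.

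**What to change.** One of two changes, made before any outcome data are seen.

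**Option A, restate as superiority.** Reword the last paragraph of the Introduction, sections 1.1 and 1.2, and the matching sentence in the Discussion, so that the trial asks whether the combined therapy is better than conventional treatment. This matches section 2.6. Add to section 2.9 that a non-significant result is inconclusive and will not be reported as equal effectiveness. The cost is wording only, with no extra patients.

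**Option B, keep the claim of equal effectiveness.** State non-inferiority on 18-week IPSS as the primary hypothesis and fix and justify a margin. Conclude non-inferiority only if the upper limit of the two-sided 95% CI for combined minus conventional lies below the margin. If it does, test superiority next in fixed sequence, which needs no adjustment of α. Restate the power at 80 evaluable per group for that margin and a justified SD. The cost is the justification of one margin and possibly more patients: at 80 per group, power is below 80% for a 2-point margin at every SD examined, and for a 3-point margin at SDs of 7 and 8.

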## 2. Study design and Methods

### 2.1. Design and setting

This RCT is a single-center, investigator-initiated study, aiming to examine the efficacy of combined therapy of acupuncture and moxibustion in treating BPH. This efficacy will be compared with that of conservative western medical treatments alone. A calculated number of 200 BPH patients will be enrolled from the Urology and the Traditional Chinese Medicine clinics of Shanghai Fourth People’s hospital. BPH patients will be randomly assigned to these two groups using a random number table in a ratio of 1:1. A block size of 4 will be generated using a computer, which ensures equal numbers of patients assigned to both groups at designated time intervals. Randomization will be stratified based on the severity of symptoms, where a total score of the baseline International Prostate Symptom Score (IPSS) <7 is considered mild, 8 to 19 moderate, and 20 to 35 severe. Written informed consent to participate in this study will be obtained from all patients. The process is shown in Figure 1.

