#### 2.2.2. Inclusion criteria

Patients will be enrolled upon meeting the following criteria:

Males of 45 years or older.BPH diagnosed upon digital rectal examination.The measured volume of the prostate ≥30 mL.The maximum urinary flow rate <15 mL/second.BPH patients are willing to participate in this study.Continuous intake of western medicines for 3 months or more.Moderate to severe BPH (IPSS score >8).

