### 2.7. Randomization

Randomization will be conducted using a random number table to assign patients to the two groups. Firstly, block size of 4 will be generated by a computer and 200 patients will be randomly assigned to the two groups in a ratio of 1:1 after acquiring their written informed consent to join a group, which ensures equal numbers of patients assigned to both groups at designated time intervals. Patients of the mild, moderate, and severe categories will be assigned equally to the two groups.

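### A single fixed block size of 4 within severity strata, at one centre with patients aware of their arm, could let a fully informed enroller foresee up to a third of allocations; the strata also need reconciling with the entry criterion

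*Protocol article*

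**What the plan says.** **Setting and allocation.** Section 2.1 of the protocol article states "This RCT is a single-center, investigator-initiated study", with patients "randomly assigned to these two groups using a random number table in a ratio of 1:1". It adds "A block size of 4 will be generated using a computer" and "Randomization will be stratified based on the severity of symptoms". Section 2.7 repeats the block size of 4 for all 200 patients. No other block size appears.

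**Strata.** Section 2.1 defines them by the baseline score: "IPSS) <7 is considered mild, 8 to 19 moderate, and 20 to 35 severe". Section 2.4.1 repeats the cut-offs for the outcome: "A total score of <7 is ranked mild, 8 to 19 moderate, and 20 to 35 severe". Section 2.7 promises balance in three classes: "Patients of the mild, moderate, and severe categories will be assigned equally to the two groups".

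**Eligibility.** Section 2.2.2 admits "Moderate to severe BPH (IPSS score >8".

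**Who knows the allocation.** Section 2.8 says that patients know their arm. It says that the investigators giving acupuncture and moxibustion, the follow-up assessors and the statistician do not, and that the two groups are managed at different times. Section 2.3 has investigators choose each control patient's drugs individually and bars acupuncture and moxibustion in that arm.

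**The concern.** In a permuted block of known, fixed size, the end of each block is determined by its beginning. The smaller the block, the larger the share of determined assignments, and among the sizes compared here (4, 6 and 8), 4 gives the largest share.

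Several features of this trial make earlier assignments easier to see than in a double-blind multicentre study. There is one hospital, the stratum follows directly from a score taken at entry, patients know their arm, and those who prescribe control drugs must know whom they prescribe for. Section 2.3 also describes a briefing before assignment in which patients are told of a choice of group, so preferences may be voiced before randomisation. An enroller who could foresee the next assignment could bring a particular patient forward or hold him back. The primary outcome is a patient-completed questionnaire, so such steering could carry into the treatment comparison. Blinded assessment later cannot undo selection that happened before randomisation.

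Separately, the strata and the entry criterion do not match, which raises the question whether every enrolled patient has a stratum.

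**Working it through.** The article states no predictability figure, so there is none to reproduce. The inputs are block size 4, ratio 1:1, one centre and 200 patients (section 2.1). I read the scheme as blocks of 4 within each severity stratum.

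**1. Assignments known with certainty, fixed block of 4.** There are six equally likely orders: AABB, ABAB, ABBA, BAAB, BABA, BBAA. An assignment is certain when only one treatment remains in the block.
- Positions 1 and 2: never certain.
- Position 3: certain when the first two match (AABB, BBAA), so 2/6 = 1/3.
- Position 4: always certain.

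Expected number per block = 0 + 0 + 1/3 + 1 = 4/3, and (4/3)/4 = 33.3%. Over 200 patients in complete blocks this is 200 × 1/3 = 66.7. Unfinished last blocks lower it slightly. With two usable strata each ending on a half block there are 49 complete blocks, giving 49 × 4/3 = 65.3, or 32.7%.

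**2. Best guess, fixed block of 4.** Always guess the arm with more places left in the block.
- Position 1: 1/2.
- Position 2: 2/3.
- Position 3: 1/3 × 1 + 2/3 × 1/2 = 2/3.
- Position 4: 1.

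The sum is 17/6 = 2.833, and 2.833/4 = 70.8%, against 50% with no information.

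**3. Larger or varying blocks.** With n per arm in a block, the expected number of certain assignments is 2n/(n+1), and the expected number of correct guesses is n + (4^n/C(2n,n) − 1)/2.

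| Scheme | Certain | Best guess |
|---|---|---|
| Fixed 4, known | 1.333/4 = 33.3% | 2.833/4 = 70.8% |
| Fixed 6, known | 1.5/6 = 25.0% | 4.100/6 = 68.3% |
| Fixed 8, known | 1.6/8 = 20.0% | 5.329/8 = 66.6% |
| 4, 6 and 8 at random | about 2.4% (simulated) | (2.833 + 4.100 + 5.329)/18 = 68.1% |

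The 2.4% comes from 1,500 simulated lists of 200. It is for an observer who knows the set 4, 6 and 8 (equally likely), sees every earlier assignment and tracks all block boundaries that fit them, but is not told the sizes used. An observer who uses only the running imbalance is certain about 0.15% of the time. The best-guess rate hardly moves because guessing the arm that is behind needs only the running imbalance, not the block size.

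**4. Strata against eligibility.**

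| Score | Class (2.1, 2.4.1) | Eligible (2.2.2) |
|---|---|---|
| 0 to 6 | mild | no |
| 7 | none | no |
| 8 | moderate | no, although the criterion is labelled moderate to severe |
| 9 to 19 | moderate | yes |
| 20 to 35 | severe | yes |

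No eligible patient can be mild, and every eligible score (9 to 35) falls in exactly one stratum.

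**The case against.** Fixed blocks of 4 are a valid way to randomise 1:1. The one-third figure requires a person who enrols patients and also knows the block size, the stratum and all earlier allocations in it. The article does not say that such a person exists. Section 2.8 states that the acupuncture investigators, assessors and statistician are unaware, and recruitment runs through two clinics, so one enroller need not see the whole sequence. Who holds the list and how it is concealed are matters that an article commonly leaves to the full protocol, so silence on them proves nothing. The remedy also barely improves the best-guess rate.

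Most of this stands. A reader might infer that a third of this trial's allocations are predictable, or that clinic staff learn each allocation; the document supports neither. One may doubt that those who deliver a treatment barred in the other arm stay unaware, but section 2.8 says they do, and trial patients are mixed with other clinic patients. What survives is narrower. Section 2.8 makes no such statement about control prescribers or recruiting staff. Concealing the next assignment would not stop someone from deducing it from a known block of 4 and visible earlier assignments.

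On the strata, a reader might infer that staff have conflicting eligibility rules or that the empty stratum damages balance. Neither follows. Only section 2.2.2 sets eligibility, and its bound is definite. An empty stratum costs no balance, and a score of 7 is ineligible in any case.

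**Conclusion.** The point holds as a conditional weakness of design and calls for a cheap improvement. It does not show that the randomisation is invalid or has been compromised. The exposure is at most 33% of assignments known with certainty, about 67 of 200, and a best guess right about 71% of the time. This assumes blocks of 4 within strata, nearly all filled, and an enroller with full knowledge of block size, stratum and history. With less knowledge the exposure is smaller, and the document does not allow the actual value to be estimated. Varying undisclosed blocks would remove nearly all certain predictions but leave the best-guess rate near 68%, so the gain lies in certainty and not in guessing.

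The mismatch between strata and entry criterion is a real contradiction in the text, but it has almost no consequence. The only score whose status is unclear is 8, and no patient enrolled under the criterion as written lacks a stratum. This part does not carry the finding.

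**What to change.** 1. Replace the single block size with randomly varying permuted blocks within strata, for example 4, 6 and 8, and do not disclose the sizes to enrolling staff. Amend sections 2.1 and 2.7 to match. If the sizes are written in a public document, the set becomes known; the 2.4% above already allows for that.

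2. Reconcile sections 2.1, 2.2.2, 2.4.1 and 2.7. Remove the mild stratum from the randomisation text, keep only strata that can be filled, and make the lower bound of the moderate stratum agree with the entry criterion, including whether a score of 8 is eligible. Which bound applies is for the investigators to settle.

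**Cost.** A regenerated list and edits to a few paragraphs. The largest possible final imbalance rises from 2 to 4 patients per stratum (half the largest block), so from 4 to 8 in total over two strata in the extreme case. That is small for 200 patients. Sample size and analysis do not change.
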